**Botulinum toxin for patients with cognitive impairment and paratonia**

**GSK-01**

**Project Summary**

**Background:** Dementia prevalence in Canada is high and projected to increase in coming decades. The economic consequences of dementia are profound with current estimates of $15 billion/yr in Canada. In addition to reduced mental capacity, these cognitively impaired, dependent individuals develop motor impairments and become increasingly immobile. The combination of increased muscle tone due to the degenerative process along with prolonged immobility, may lead to fixed contractures that cause the individual pain and discomfort, put them at risk for skin breakdown, and interfere with the ability to receive care. Preliminary work has suggested that in those with increased tone that interferes with the provision of care, administration of Botulinum toxin to select muscle groups, reduces time taken to administer hygiene, decreases effort and exertion by staff, and reduces the discomfort of the patient.

**Objective:** Perform a pilot study to assess the impact of Botulinum toxin type A on muscle tone, time to provide care, and carer burden in individuals who are cognitively impaired and fully dependent.

**Methods:** *Trial design:* The study will be ablinded, placebo-controlled, randomized trial with a crossover design with two treatment cycles of 16 weeks each. Following baseline assessment and injections, repeated assessments will take place at 2, 6, 12 and 16 weeks post injections.

*Intervention*: Subjects will be randomly allocated to receive either active Botulinum toxin injections at baseline or 16 weeks or control sterile saline injections at the alternate injection period. The patient, professional caregiver and study investigators involved in assessments will be blinded to treatment allocation.

*Setting*: The trial will take place ata spasticity management clinic with infrastructure (personnel, equipment, and space) and experience for safe and efficacious administration of Botulinum toxin injections.

*Subjects:* 10 fully dependent patients with cognitive impairment that have increased upper extremity tone interfering with the provision of care.

*Outcome measures*: The primary outcome measure will be the Carer Burden Scale assessing ease of administering care that includes aspects of providing hygiene and dressing. Secondary outcome measures will include the Modified Ashworth Scale (MAS) objectively measuring increased tone, time taken to perform tasks (morning care routine) before and after treatment, and the caregiver Visual Analogue Scale (VAS) assessing perception of ease of care-giving, nurse-investigator and professional and caregiver Global Assessment Scale (GAS) assessing overall response to treatment. The Pain Assessment in Advanced Dementia (PAINAD) instrument will be used to assess whether treatments reduce pain in patients when having morning care performed. Video-recordings of morning care routines prior and following treatments will be reviewed and compared to ensure reliability. Additionally, the caregiver will be questioned in an open-ended format to determine what additional factors contributed to relevant changes in the care of patients as a result of the injections that may not have been captured with quantitative measures.

**Statistical Analysis:** The proposed crossover design warrants the use of mixed regression modeling techniques in order to isolate the effect of Botulinum toxin, relative to placebo on the described outcomes. Treatment effects will be defined as the change in relevant scores from baseline to 6 weeks, and 16 to 22 weeks (i.e., change from baseline until 6 weeks post-treatment or placebo).

**Conclusions:** In these times of fiscal constraint, difficult decisions regarding resource allocation to optimize patient care need to be made. An intervention with the capacity to reduce care burden, improve standard of care, and potentially increase patient and caregiver quality of life, would be an attractive strategy. Preliminary experience suggests that Botulinum toxin injections may result in this effect. This pilot study will assess the feasibility of conducting a larger study that will evaluate the impact and cost-effectiveness of reduction of tonein cognitively impaired, fully dependent individuals.

.

**Proposal**

**Objectives:**

Perform a pilot study to assess the impact of Botulinum toxin type A on muscle tone, time to provide care, and carer burden in individuals who are cognitively impaired and fully dependent.

**Background:**

Dementia is highly prevalent in Canada: an estimated 1.5% of all Canadians live with dementia (nearly 500,000 people). A new case is diagnosed approximately every 5 minutes. It is projected that by 2038, due to population ageing, the prevalence of dementia will be 2.8% with a new case being diagnosed every 2 minutes (1). A 1994 Canadian study of health and aging estimated that the prevalence of dementia in those over the age of 65 was ~ 8% with approximately 50% of these individuals lived in long-term care settings (2). Further, 62% of long-term care residents met criteria for dementia (3).

The economic consequences of this disease are profound both in terms of financial and caregiver burden. The current costs of dementia to the Canadian economy are estimated at $15 billion per year, and by 2038 that cost is projected to be $153 billion (1). A study assessing the economic burden of Alzheimer’s disease calculated the costs of caring for an institutionalized, severely cognitively impaired person to be approximately $2.5 billion in the US in the year 2000 with a projected tripling of these costs by 2040 (4). In 2000, Canada spent a remarkable 1.06% of its GDP to finance costs of long-term institutionalized care (5).

In addition to cognitive deterioration, dementia is often accompanied by motor disability that amplifies caregiver burden. Immobility in demented individuals is due in part to paratonia, a form of increased tone first observed by Dupre, in 1910, that he characterized as “an inability to relax muscles in the setting of cognitive impairment” (6). Postulated to originate in the central nervous system, paratonia exerts its effects by increasing muscle resistance. In advanced stages of dementia, it is associated with reduced mobility and the development of fixed postures (contractures). Paratonia has been estimated to be present in 5% of those with mild cognitive changes and 100% in those with advanced dementia (7-10).

It is commonly accepted that once contractures have developed, medical treatments are futile and for these unfortunate individuals, families and care-givers, management strategies must be found that take into account these limitations. The consequences of fixed postures include difficulty accessing body regions to provide hygiene which increases caregiver burden, and reduces quality of provision of care resulting in consequences such as infection or skin breakdown. Additionally, the individual receiving care may experience discomfort and pain as a result of efforts to manipulate fixed limbs.

**Rationale for Study:**

Botulinum toxin type A (Botox™, Xeomin™) is an exotoxin produced by the bacterium *Clostridium botulinum*. It can be used as a therapeutic intervention to selectively weaken skeletal muscle in a dose-related manner by impairing the release of acetylcholine, a neurotransmitter, at the neuromuscular junction (11). While commonly used for cosmetic purposes to reduce wrinkles, it has found therapeutic indications in people with abnormal muscle tone. Currently, it is the approved treatment of choice in Canada for conditions including blepharospasm, strabismus, hemifacial spasm, cervical dystonia, spasmodic dysphonia, and foot deformity in cerebral palsy patients. Botulinum toxin has also been proven safe and effective for the treatment of post-stroke spasticity. In stroke patients with spasticity, it reduces tone and improves the capacity to independently perform activities of daily living (ADLs)(12); in those requiring full care due to disability following stroke, administration of Botulinum toxin has been shown to reduce caregiver burden (13). Injections are well tolerated and are effective for approximately 3 months. Side-effects are minimal due to the fact that Botulinum has local and not systemic effects, with none of the systemic consequences that limit the use of orally administered agents for tone reduction. For patients with spasticity due to multiple sclerosis, the addition of a physical therapy regimen has been shown to further augment the effects of Botulinum toxin on tone reduction with improved function (14).

There is a growing consensus that this intervention should be applied early post-stroke, as a first-line treatment to reduce or prevent disability that may occur as a result of prolonged immobility (15). By reducing increased tone due spasticity following stroke, rehabilitation is facilitated, preventing permanent contractures and related sequelae. Similarly, it could be extrapolated that patients with paratonic rigidity may experience benefit from early administration of Botulinum toxin, which should facilitate provision of care by preserving range of motion, thereby delay onset of contractures.

To date, studies have not been performed to evaluate the efficacy of Botulinum toxin injections for paratonia. However, the profoundly detrimental impact on patient and caregiver quality-of-life as a result of immobile limbs in individuals with dementia has prompted us to offer Botulinum toxin injections to a small cohort of patients evaluated for this indication at the Elkie Adler Spasticity Management Clinic. We have found that common postures that occurred in the arm and were amenable to improvement through Botulinum toxin injections included: adducted shoulder, flexed elbow, wrist, and fingers, and a thumb-in-palm deformity, similar to postures following stroke. Such postures interfere in the provision of care and/or result in pain or skin breakdown, and diminish quality of life for patients and caregivers. Administration of Botulinum toxin in these few patients resulted in increased ease of care, decreased time to perform care, improved skin integrity, and reports of reduction in caregiver burden and patient discomfort when hygiene and morning care (defined as the period of time between 7:00 am and 12:00 pm when caregivers are engaged in activities related to bathing, grooming, dressing and toileting(16)) were administered. As such, we hypothesize that dependent individuals with dementia and increased tone resulting in involuntary postures may benefit from treatment with Botulinum toxin injections.  We propose to conduct a pilot study to test the above hypothesis, and to refine the approach to Botulinum toxin use in this context, in preparation for subsequent prospective studies.  The ultimate objective of a phase III trial would be to prove that Botulinum toxin injections are efficacious, safe and cost-effective in reducing burden of care and improving standard of care for fully dependent, cognitively impaired individuals with increased tone interfering in care.

**Pilot study objectives**

*Primary Objective*:

1. Confirm proof of principle that paratonic rigidity and its consequences can be reduced with Botulinum toxin injections resulting in reduced caregiver burden.

*Secondary Objectives:*

1. Determine optimal time points for evaluation of efficacy in this patient
   population and whether this time period is sufficient for washout of Botulinum toxin effect
2. Determine most salient and sensitive outcome measures
3. Identify obstacles in data gathering
4. Determine feasibility of battery of assessments in this pilot study that will eventually be used in a future phase III study

**Methods**

*Trial design:*

We propose a randomized, double-blind, placebo-controlled, crossover trial design. All subjects will thus act as their own controls. There will be 2 cycles of injection: at baseline and at week 16. All subjects will be randomized to receive active Botulinum toxin injection or sterile saline injections and will receive the alternate substance at the subsequent injection. The investigator assessing outcome, the study subject and the professional caregiver (primary nurse) will be blinded to treatment allocation.

*Setting:*

The Elkie Adler Spasticity Management Clinic is composed of a multidisciplinary team of physiatrists, neurologists, physical and occupational therapists, clinical nurse specialists, a social worker and a kinesiologist. There is a seating Clinic and an assistive communication device program on-site. It is located at Baycrest, in Toronto, Ontario, a geriatric-focused institution with an affiliated retirement home, nursing home and chronic-care hospital, as well as outpatient specialty Clinics. The mandate of the Clinic is to provide a multi-disciplinary team approach to patients with disabilities in order to address every aspect of their activities of daily living and to enable them to optimize their full potential to live independently and in comfort.

*Participants:*

Ten individuals with severe cognitive impairment, requiring total care for basic activities of daily living (ADLs), and having increased tone in an arm, that is interfering with the provision of care will be included in the study. If bilateral limbs are affected, only one (the more severely affected) limb will be injected.

Subjects will be eligible for the study if they have a score ≥3 (considerable resistance to passive movement) on the Paratonia Assessment Instrument (PAI) in an affected limb, and which results in one or more of: (i) difficulty in provision of morning care; (ii) postures resulting in pain when flexing, extending or abducting the limb; or (iii) postures resulting in skin breakdown or resulting in pressure ulcers. Exclusion criteria will include the presence of an alternate etiology for increased tone (ie., parkinsonian syndromes manifesting rigidity, known strokes or other focal neurological deficits), fixed contractures of the affected limb (assessed clinically as no mobility on passive range of motion), or injection with Botulinum toxin in the preceding 6 months.

*Intervention:*

Muscles to be injected and exact doses injected will be determined based on the characteristics of the posture causing disability (amount of increased tone, size of muscle) using EMG-guided muscle exploration at the time of injection with an upper dose limit of 300U based on doses used in other upper-limb spasticity studies (12, 15, 17). Injection sites within the muscle will be determined according to surface landmarks for motor end-points as specified in a standard text of neuromuscular anatomy (18).

*Study procedure:*

**Randomization**

The choice of the first injection will be made by consulting a table of random numbers that will be determined by the pharmacy representative at Baycrest Hospital that will be part of the study team. The pharmacist will be responsible for the all allocation codes and preparation of the Botulinum toxin and placebo syringes, and distribute these accordingly to the treating physician.

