**Statistical Analysis**

*Power calculations*

[figure not shown]
Power calculations performed using the xsampsi application for sample size and power in crossover trials (Stata v. 11.0) were used to create the figure below. Assuming 10 unique individuals are recruited into the study, we will have 70-80% power to detect mean changes of between 0.5 and 1.5 points on a 5 point Likert scale, under different assumptions regarding the standard deviation in such measurement (SD 0.5, 1, 1.5 or 2). As such, we expect to be able to detect clinically meaningful changes in measurement with treatment even with the relatively small sample size anticipated in this pilot study. Data collection will permit further refinement of power and sample size calculations for future, larger trials if effects observed here are promising.

*Statistical Analysis*

Because of between patient variability in the affected area injected and severity of paratonia, and because of our desire to control for period and ordering effects we will use mixed regression models for analyses of quantitative outcomes, in order to isolate the effect of Botulinum toxin relative to placebo. Mixed models as applied to crossover designs permit adjustment for treatment sequences (i.e., Botulinum toxin first vs. second), period effects (i.e., first injection vs. second injection), between individual variation in severity and response to therapy, etc. We will estimate treatment fixed effects (i.e., effect of Botulinum toxin treatment), defined as the change in relevant scores from baseline to 6 weeks, and 16 to 22 weeks (i.e., change from baseline until 6 weeks post-treatment or placebo). Because of the anticipated variability in severity of paratonia in individual patients, and variability in responses of caregivers to patient disability, we will treat individual patient/caregiver dyads as model random effects.

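### No balancing of the two injection orders is described for 10 patients; read as simple randomisation, this costs about 15% in variance on average, and one sentence avoids it

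*Protocol*

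**What the plan says.** The Protocol, Methods (Trial design), sets out a two-period, two-order crossover: "All subjects will be randomized to receive active Botulinum toxin injection or sterile saline injections and will receive the alternate substance at the subsequent injection". No allocation ratio for the two orders is given there.

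Under Randomization, the order is set as follows: "The choice of the first injection will be made by consulting a table of random numbers", a table "that will be determined by the pharmacy representative at Baycrest Hospital". The same section makes the pharmacist responsible for all allocation codes. It does not mention blocks, a fixed list or any other restriction, and it does not say that allocation is unrestricted.

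Under Statistical Analysis, the sample size enters as "Assuming 10 unique individuals are recruited into the study", and the claim is that "we will have 70-80% power to detect mean changes of between 0.5 and 1.5 points on a 5 point Likert scale" for assumed SDs of 0.5, 1, 1.5 or 2. No alpha, split between orders, within-patient correlation or dropout allowance is stated. Mixed models are chosen partly "because of our desire to control for period and ordering effects", with patient/caregiver dyads as random effects. The outcome is the 6-week change from the start of each cycle.

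**The concern.** Every patient receives both treatments, so information on the treatment effect comes from within-patient differences. Once period is in the model, the effect is estimated by comparing those differences between the two orders, and its variance depends on how many patients are in each order. With only 10 patients, independent draws from a random-number table often give unequal groups.

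Precision is at stake in a trial that claims no more than 70-80% power and states no reserve for dropout. A secondary objective, whether the interval is long enough for washout, is also affected. Only toxin-first patients can show toxin effect carrying into the placebo cycle, and an 8:2 split could leave two of them.

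**Working it through.** **Inputs.** From the Protocol: 10 patients, two orders, and adjustment for period and sequence. Assumed, because not stated: simple randomisation with probability 1/2 for each order, two-sided alpha of 0.05, and no dropout.

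**The plan's own figure.** The period-adjusted effect is half the difference between the two order means of the within-patient period difference. Its variance is (SDd²/4)(1/n1 + 1/n2), where SDd is the SD of that within-patient difference. At 5:5 the standard error is SDd × √(0.4)/2 = 0.316 SDd. Power comes from the noncentral t with 8 df.

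- If the stated SD means SDd, a change equal to the SD has 79.1% power (88.5% by the normal approximation). This fits the claim for 0.5, 1.0 and 1.5 points at SDs of 0.5, 1 and 1.5. At SD 2, a change of 1.5 has 55% (66% normal).
- If the stated SD is for one measurement with zero correlation, a change equal to the SD has 50%.

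The 70-80% therefore cannot be uniquely reproduced, so 80% at 5:5 is used below as an assumed starting point. The variance ratios need neither the SD nor the correlation.

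**Split of 10 patients.** The probability of k patients in one order is C(10,k)/1024. The variance relative to 5:5 is (1/n1 + 1/n2)/0.4.

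| Split | Probability | Relative variance | SE increase | Power if 80% at 5:5 |
|---|---|---|---|---|
| 5:5 | 252/1024 = 24.6% | 1.000 | 0 | 80.0% |
| 6:4 | 420/1024 = 41.0% | 1.042 | 2.1% | 78.4% |
| 7:3 | 240/1024 = 23.4% | 1.190 | 9.1% | 72.9% |
| 8:2 | 90/1024 = 8.8% | 1.563 | 25% | 61.3% |
| 9:1 | 20/1024 = 2.0% | 2.778 | 67% | 39.4% |
| 10:0 | 2/1024 = 0.2% | not estimable | – | – |

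**Cumulative.**
- 5:5 or 6:4: 672/1024 = 65.6%.
- 7:3 or worse: 352/1024 = 34.4%.
- 8:2 or worse: 112/1024 = 10.9%.

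**Averages.**
- Mean relative variance over the estimable splits: (252×1 + 420×1.0417 + 240×1.1905 + 90×1.5625 + 20×2.7778)/1022 = 1.146. The mean SE ratio is 1.065.
- Average power, counting 10:0 as zero: (252×0.800 + 420×0.784 + 240×0.729 + 90×0.613 + 20×0.394)/1024 = 0.751.
- From the lower end of the plan's range, 70% at 5:5, the powers from 6:4 to 9:1 are 68.3%, 62.5%, 51.3% and 32.2%. The same weighting gives about 65%.

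**The case against.** **Lack of balance is inferred from silence.** This stands. A random-number table can equally be used to shuffle a restricted list, and the pharmacy sets the table. A reader might infer that the protocol prescribes unrestricted allocation, but it does not say so. What can be said is that no balancing is described, and that one draw per patient is the natural reading.

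**The usual loss is small.** This also stands. The most likely split is 6:4, which costs 1.6 power points. The 15% average is driven by the tail: 8:2 and 9:1 together are 110/1024 = 10.7% of draws but supply (90×0.5625 + 20×1.7778)/149.4, about 58%, of the excess variance. A reader might take 39% power or complete confounding of treatment with period as the expected result. Those cases have probabilities of 2.0% and 0.2%.

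**Progressive dementia does not by itself produce a period effect here.** A reader might argue that it does. The outcome is the change from each cycle's own baseline, and steady decline adds the same 6-week change to both cycles. Only non-constant drift would differ between periods. The point does not need such an effect: the plan adjusts for period regardless, and that adjustment carries the variance cost.

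**This is a pilot study.** True, and it limits the weight of the point. It does not remove the case for avoiding a loss that buys nothing.

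**Conclusion.** The point holds as a cheap improvement in precision. On the natural reading, the planned period-adjusted effect carries an average variance penalty of about 15%. The loss is minor in about two thirds of draws, material in about one third and large in about one ninth. Average power is about 75% against an assumed 80% at 5:5.

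These figures rest on simple randomisation with equal probabilities and 10 completers; the power figures also need two-sided alpha of 0.05 and the assumed starting power. If the pharmacy already intends a 5:5 list, there is no loss and only the wording needs correcting.

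A reader might also infer bias from unequal orders. The documents do not support that, because period is in the model; imbalance widens the interval and does not shift the estimate.

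**What to change.** In the Protocol, Randomization, replace the sentence on the random-number table with a statement that the pharmacist uses the table to permute a list of exactly five toxin-first and five placebo-first codes, held only in the pharmacy. This brings the relative variance at allocation to 1.00 with no extra patients or visits. The pharmacist already holds all codes, so no new arrangement is needed.

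There are two small limits. Once one order is used up, the remaining codes are determined: on average 5/6 + 5/6, about 1.7 of 10. This matters only if earlier codes have been broken, for which the Blinding and Side Effects sections make provision. Equal allocation also does not guarantee equal completers, so the realised split should be reported.
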